### Embedded qualitative component

A qualitative descriptive approach [49] will be taken for the qualitative component of the study. A sample of ten participants from the intervention group will be invited to take part in an audio-recorded, one-to-one semi-structured interview within one month of intervention completion. An interview guide will be developed using established guidance [50, 51] and will explore the participant’s experiences of receiving the intervention, the feasibility and acceptability of the intervention, and the perceived effects of the intervention, including potential AEs. The researcher will explore the participant’s adherence to the programme and any adaptations made to it, as well as the acceptability of the recruitment, consent and outcome assessment processes of the study. The interview will also examine the factors which could facilitate or hinder participants in maintaining their PA levels. These could include environmental factors, personal factors or support from care staff.

Staff from the intervention site will also be invited to take part in a one-to-one semi-structured interview, within one month of intervention completion. A variety of staff (manager, nurse, care staff) will be sought in order to maximise variation in the sample. Staff will be included if they have had a role in recruitment or delivery of the intervention. The interview will explore the staffs’ role and experiences of being involved in the study, including their participation in the staff education sessions and the monitoring of the PA programmes. It will also explore the staff’s perceptions of the potential for sustaining the PA programme within the nursing home following the study.

Semi-structured qualitative interviews will be conducted with a small subset of participants from the control group. It will focus on obtaining a description of usual care and evaluating participant’s experiences during recruitment.

### Statistical analysis

#### Quantitative analysis

The data analysis software SPSS Statistics (24.0 for Windows, Chicago, IL, USA) will be used to manage and analyse quantitative data. Feasibility data will be collated using descriptive statistics and, where relevant, evaluated against progression criteria. Demographical information in both groups will be tabulated and summarised. The effect of the intervention on clinical outcomes will be examined using suitable numerical and graphical summaries. The statistical analysis will serve primarily to provide an estimate of the likely effect size and variability of the response within an individual over time. This, as well as the mean and standard deviation of the primary outcome measure at baseline and the participant attrition rate, will enable a more accurate sample size calculation for a definitive RCT. All within- and between-group outcome analyses will be treated as preliminary and interpreted with caution.

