**Primary research questions**	
Is the intervention feasible and acceptable to staff and participants? • Is the time commitment required for staff to monitor the intervention and participants to partake in the intervention feasible? • Are there any environmental barriers to completion of the intervention? • Is the content of the intervention acceptable to participants and staff? • Do the participants adhere to the intervention and what adherence issues arise? • What are the components of usual care for participants allocated to the control group?	
Are the outcome measures feasible and acceptable to participants? • What is the required time and number of visits required to collect each outcome from participants? • Are the outcome measures acceptable to participants? • What is the level of missing data within the self-reported outcome measures? • What is the feasibility of collecting health economic data (i.e. sources used and time taken)?	
What is the required sample size for a definitive RCT? • What is the baseline score and variability of the primary outcome measure among participants? • What is the estimated effect size and variance for the primary outcome measure? • What are the recruitment and attrition rates for nursing homes and participants? Do these rates differ between the intervention and control groups?	

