## Methods

### Design and setting

A randomised controlled pilot feasibility study, with embedded qualitative and economic components, will be carried out. Two nursing homes will take part in the study; participants in one nursing home will receive the PA intervention and participants in the other will receive usual care. In order to avoid contamination between intervention and control groups, randomisation will take place at nursing home level [12]. The pilot feasibility study will not be an exact scale model of a definitive RCT, the difference being that follow-up outcome assessment will not be blinded as a full analysis of outcome data is not intended. However, the recruitment, randomisation, assessment and intervention conditions will be similar to a definitive RCT in order to answer the feasibility research questions. Figure 1 provides a CONSORT flow diagram displaying the movement of participants throughout the study. A schedule for enrolment, interventions and assessments is displayed in Fig. 2. The protocol adheres to the Standard Protocol Items Recommendations for Interventional Trials (SPIRIT) guidelines (Additional file 1) [21] and the SPIRIT-Patient Reported Outcomes Extension [22].

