### Sample size calculation

An objective of this study is to assess the feasibility of recruiting and retaining the required number of participants per nursing home which would be needed in a definitive RCT. Therefore, the sample size calculation for this pilot feasibility study is based on the estimated power calculation for a definitive cluster RCT using the primary outcome measure, the Timed Up and Go (TUG) test [23]. In the absence of normative TUG data for an Irish cohort of older adults living in nursing homes, sample size calculations for a definitive RCT were estimated using a New Zealand sample of older adults living in residential care [12]. The sample size requirements for a definitive RCT were calculated as being a minimum of four clusters of size 20 in each arm, in order to have 80% power (α = 0.05) to detect a mean change in TUG score of 4.7 s (± 6.8 s). The current study will recruit one nursing home for each arm. The desired number of participants in each nursing home will be maintained as 20 in order to assess the recruitment potential, recruitment time and feasibility of delivering the intervention to this number of participants. The number of participants lost to follow-up per nursing home will be recorded to inform the final numbers needed when recruiting to the definitive RCT.

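### The pilot's TUG effect size is named as an input to the definitive sample size, but with one home per arm it is confounded with the home and has no valid standard error, and the pilot yields no usable ICC

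*Protocol article*

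**What the plan says.** Table 1 makes the size of the definitive trial a primary research question and lists under it "What is the estimated effect size and variance for the primary outcome measure". The Quantitative analysis section says the statistical analysis "will serve primarily to provide an estimate of the likely effect size and variability of the response within an individual over time". It adds that this, together with the baseline mean and SD of the primary outcome and the participant attrition rate, "will enable a more accurate sample size calculation for a definitive RCT".

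The design is fixed elsewhere in the article. Under Design and setting, "randomisation will take place at nursing home level". Under Sample size calculation, "The current study will recruit one nursing home for each arm" and "The desired number of participants in each nursing home will be maintained as 20". The pilot's size is "based on the estimated power calculation for a definitive cluster RCT using the primary outcome measure", the TUG. That calculation arrives at a "minimum of four clusters of size 20 in each arm, in order to have 80% power" at alpha 0.05, for a mean change of 4.7 s with 6.8 s as the spread, taken from a New Zealand residential-care sample. No ICC or design effect is stated there. None is listed among the quantities that the pilot is to supply.

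**The concern.** When one home receives the programme and one home does not, arm and home are the same variable. A between-arm difference in TUG may come from the programme, from anything else that differs between the two homes, or from an assessor who knows the allocation. No analysis of these data can separate the three. The number of homes in a cluster trial also depends heavily on between-home variation, and two homes say almost nothing about that.

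The article nevertheless gives the effect estimate a role in sizing the definitive trial and says that the result will be more accurate. If the pilot difference were put into the sample size formula, a chance or home-driven error would carry through as its inverse square. The ICC would remain an untested assumption while appearing to have been updated from local data.

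**Working it through.** **Inputs from the article (Sample size calculation).** Difference 4.7 s, SD 6.8 s, alpha 0.05 (taken as two-sided; the article does not say), power 80%, 20 residents per home, four homes per arm in the definitive trial, one per arm in the pilot. **Assumed:** the ICC, because none is stated. I treat 6.8 s as the SD of the analysed TUG measure; the article attaches it to a mean change.

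**1. The article's own figure.** Without clustering, n per arm = 2 × (1.96 + 0.842)² × 6.8² / 4.7² = 32.9, so 33. With 20 per home the design effect is 1 + 19 × ICC. Eighty per arm allows a design effect up to 80/32.9 = 2.43, an ICC of (2.43 − 1)/19 = 0.075 to 0.076. Three homes per arm would be enough up to an ICC of about 0.043. By the normal approximation, then, four homes correspond to any ICC from about 0.043 to about 0.075. With a t test on 2 × (4 − 1) = 6 degrees of freedom, four homes of 20 give exactly 80% power at an ICC of 0.036. The figure of four homes cannot be reproduced without an ICC, but it fits values in this region. I use 0.036 and 0.076 as the illustrative pair.

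**2. How much the unstated ICC matters.** Power of four homes of 20 per arm:

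| ICC | Normal approximation | t on 6 df |
|---|---|---|
| 0.02 | 96% | 87% |
| 0.05 | 88% | 74% |
| 0.10 | 73% | 58% |

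**3. What the pilot can say about the ICC.** Between-home, within-arm degrees of freedom are 2 × (1 − 1) = 0 once the intervention has started. Baseline is completed before allocation is revealed, so two homes give 1 degree of freedom for a baseline ICC. With 20 per home and an observed ICC of 0.05, F = 1 + 20 × 0.05/0.95 = 2.05 on 1 and 38 df, and the 95% interval for the ICC runs from below 0 (−0.03) to 0.99. This is of no use for planning.

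**4. Sampling error of the pilot effect.** For one home of 20 per arm, SE = 6.8 × √(2/20 × (1 + 19 × ICC)).

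- ICC 0.036: 6.8 × √(0.1 × 1.69) = 2.8 s, so 95% sampling error is about ±5.5 s.
- ICC 0.076: 6.8 × √(0.1 × 2.43) = 3.4 s, so about ±6.6 s.

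Both half-widths exceed the 4.7 s target. These standard errors are computed from an assumed ICC; the pilot data could not supply them. An analysis ignoring the home would report about 2.1 s whichever ICC is true.

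**5. Effect on the definitive sample size.** Required n is proportional to 1/difference² (SD and ICC held fixed, ignoring the change in degrees of freedom). Suppose the true effect is 4.7 s and the pilot estimate replaces it:

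- One SE too high: (4.7/7.5)² = 0.39 to (4.7/8.05)² = 0.34 of the required n.
- One SE too low: (4.7/1.9)² = 6.1 to (4.7/1.35)² = 12.1 times the required n.

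This counts sampling error only. Assessor bias would add to it.

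**6. What the pilot can estimate.** A pooled within-home SD has 38 df. If it came out at 6.8 s, its 95% interval would be 5.6 to 8.8 s: imprecise, but a proper estimate. The baseline to follow-up correlation and the attrition rate can also be estimated within homes.

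**The case against.** The strongest reply is that this is a feasibility study which says so repeatedly. Design and setting states that no full outcome analysis is intended, Quantitative analysis calls outcome comparisons preliminary, and the Discussion names the small number of homes as a limitation. These cautions are real, but none says that effect and home are confounded, and none withdraws the sizing role given in Table 1 and Quantitative analysis.

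Several narrower objections stand and limit the point:

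- The accuracy claim is relative to the New Zealand planning data. Local SD, within-person variability and attrition do improve on those data, so a reader who concludes that the whole claim fails goes too far.
- TUG is measured at baseline and twice afterwards, and the abstract plans linear mixed models. Stable home differences can therefore be largely removed, and adjustment could shrink the standard errors above. Differential change by home stays confounded with treatment.
- It is tempting to say that between-home variance has no degrees of freedom at all. At baseline there is nominally one; it is merely useless. Nor does the article claim that it will estimate an ICC.
- A reader might infer that a misleading effect could stop the definitive trial. The article does not support this: the Table 5 criteria concern recruitment, recruitment time, retention and adherence, and none uses TUG.
- The article does not say that the pilot difference will simply replace 4.7 s. The multipliers show what would follow if it did.

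**Conclusion.** The point holds for two quantities only. The pilot's between-arm TUG difference is treatment effect plus home difference (or differential change by home) plus possible assessor bias, without a valid standard error, so it cannot make the definitive sample size more accurate. The same is true of between-home variance, for which the pilot has at best one degree of freedom. The claim is sound for TUG SD, within-person variability or correlation, and attrition.

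The size is illustrative: with SD 6.8 s and ICC 0.036 to 0.076, a standard error of about 2.8 to 3.4 s, and a definitive sample between about one third of what is needed and about 6 to 12 times it for an error of one standard error. A different ICC or a baseline-adjusted SD changes these figures but does not remove the confounding. This should be fixed rather than must be fixed, because the feasibility aims and the progression decision are unaffected.

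**What to change.** In Table 1 and in Quantitative analysis:

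- Remove the pilot effect size as an input to the definitive sample size, and say that it will be reported descriptively only.
- State that the definitive trial will be sized on a prespecified TUG difference, justified as important. The article never describes 4.7 s in those terms, so keeping that value would need its own justification.
- Name what the pilot will supply: the pooled within-home SD of TUG with its upper confidence limit, the baseline to follow-up correlation, and attrition.
- State that the ICC will come from external sources as a range, that power will be calculated with degrees of freedom based on homes, and that this pilot cannot usefully estimate the ICC.

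The cost is wording; no extra data or homes are needed. The only loss is that the pilot no longer offers an effect size for planning.

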#### Qualitative analysis

Participant and staff interviews will be transcribed verbatim. NVivo qualitative data analysis software (QSR International Pty Ltd., Version 11, 2015) will be used to assist in qualitative data analysis and management. The data will be analysed thematically, guided by the six-stage framework outlined by Braun and Clarke [52]. The data will be initially coded according to the participants own words and these will be sorted into preliminary broad themes. These will then be revised and refined to ensure that there is sufficient distinction between themes and coherence within themes [52].

## Discussion

A large proportion of previous research has implemented PA interventions through an exercise class delivered by exercise specialists and containing specific types of exercises (e.g. muscle strengthening, range of movement, flexibility and balance) [7, 9, 10]. This approach is restrictive for residents as it confines PA to within designated sessions and limits uptake as nursing home staff generally do not have the same expertise as exercise specialists in delivering and monitoring these specific types of exercises. The current protocol will evaluate the feasibility and acceptability of a functionally based, personalised PA intervention embedded into the daily routines of older adults living in nursing homes. If ultimately successful in a large-scale RCT, this may provide an effective and cost-effective means of integrating resident PA into routine clinical practice within the nursing home setting.

The strengths of this study include its clear research questions and provision of criteria for progression to a full-scale RCT, as well as the collection of quantitative, qualitative and economic data in order to gain a comprehensive overview of the intervention. This study will include people with cognitive impairment including people with dementia, thereby increasing the generalisability of the study, as a large proportion of nursing home residents have some level of cognitive impairment [53]. Importantly, this also ensures that people with cognitive impairment are not excluded from research which may potentially benefit their health.

A limitation of the study is the lack of assessor blinding to groups during follow-up outcome assessment. This approach was chosen as the primary aim of the study is to evaluate feasibility and acceptability, rather than to establish concrete effectiveness data. As such, this approach will enable the researcher to gain practical experience of applying the outcomes in this population and to uncover any practical issues which may arise. The preliminary outcome data should be therefore interpreted with care. This study, albeit a pilot feasibility study, is also limited by the small number of nursing homes involved. The subjective means of measuring adherence to the intervention using an exercise diary, as opposed to more objective measures (e.g. video cameras), is a further limitation to the study.

Research involving older adults is important and necessary to better enable the effective management of the ageing population. The findings of this study will be disseminated in peer-reviewed journals and presented at national and international conferences.

### Trial status

Protocol version 6. Recruitment began in March 2018 and will end in June 2018.

## Abbreviations

DON: Director of Nursing
GP: General practitioner
ICECAP-O: The Investigating Choice Experiments for the Preferences of Older People Capability index
MMSE: Mini Mental State Examination
PA: Physical activity
RCT: Randomised controlled trial
SMART: Specific, measurable, achievable, realistic and timely
SPIRIT: Standard Protocol Items Recommendations for Interventional Trials
TUG: Timed Up and Go test
WHO: World Health Organization
